**Methods:**

This study will be a prospective, pragmatic, pilot randomised controlled trial comparing a standard care group (low-intensity aerobic exercise) and a moderate-intensity resistance training group. Participants aged 18 years and older with coronary artery and/or valve disease requiring surgical intervention will be recruited pre-operatively and randomised 1:1 to either the resistance training or standard care group post-operatively. The primary outcome, cognitive function, will be assessed using the Alzheimer’s Disease Assessment Scale and cognitive subscale. Secondary measures include safety, feasibility, muscular strength, physical function, multiple-domain quality of recovery, dynamic balance and patient satisfaction. Assessments will be conducted at baseline (pre-operatively) and post-operatively at 2 weeks, 8 weeks, 14 weeks and 6 months.

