### Objectives

This study aims to examine the effect of moderate-intensity resistance training compared to a control group who receive standard cardiac rehabilitation involving low-intensity aerobic training within the community setting on post-operative cognitive recovery following cardiac surgery via median sternotomy. The safety, feasibility, patient satisfaction and effect of the exercise interventions on overall post-operative recovery, muscular strength, balance, lung capacity, upper limb function, independence with activities of daily living and anthropometry will also be examined. As this is a pilot study, the data obtained will be used to inform a sample size calculation to be performed for a larger definitive study.

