#### Secondary outcomes

##### Safety and feasibility

Recruitment rate and retention rate will be analysed to determine study feasibility. Feasibility data will be analysed as follows: recruitment rates and patient recruitment-to-screening ratio, percentage of participants who complete the intervention, overall percentage of sessions attended and number of participants who drop out of the study. Data for safety will be analysed as the number of sessions and exercises stopped due to pain, any adverse event or incident that stops the participant from completing the prescribed exercise, and any major adverse cardiac and cerebral events (MACCE). MACCE endpoints include all-cause mortality, cerebral vascular event (stroke), documented myocardial infarction or repeat coronary intervention (percutaneous coronary intervention or redo cardiac surgery), with data being collected at the 6 months.

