### Data analysis

The objective of this pilot study is to test the feasibility of recruitment, retention, intervention and data collection, and the safety of moderate-intensity resistance training, on post-operative cognitive and functional recovery. The following parameters would indicate clinically important relative differences between groups:
Group separation: ≥ 20% difference between groups;Feasibility: screening-to-recruitment ratio < 2 and recruitment of ≥ 1 participant/site/week;Safety: adverse events and serious adverse events;Protocol compliance: ≥ 80% protocol compliance and exercise intervention commenced at two post-operative weeks;ADAS-cog: difference of at least 2 on the ADAS-cog scale; andMuscular strength: ≥ 15% improvement in strength.

The analysis will be on an intention-to-treat basis. Data collected for feasibility and safety will be analysed using descriptive statistics (mean ± standard deviation) to explore possible effects of the intervention. Mean changes in outcomes over time will be summarised graphically and descriptively within each group, with odds ratio and confidence intervals. As this is a pilot study, it is not powered to detect clinically meaningful effects. Feasibility data will be analysed to determine whether it is worth conducting a large-scale trial. A statistician not involved in the study and the student researcher will assess these parameters at the end of the trial.

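### An odds ratio attached to within-group mean changes does not fit the ADAS-cog or the other scores, and mean ± SD does not suit event counts

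*Protocol article*

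**What the plan says.** All references are to the protocol article.

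- **Outcomes over time** (Data analysis): "Mean changes in outcomes over time will be summarised graphically and descriptively within each group, with odds ratio and confidence intervals".
- **Feasibility and safety** (Data analysis): "Data collected for feasibility and safety will be analysed using descriptive statistics (mean ± standard deviation) to explore possible effects of the intervention".
- **Type of feasibility and safety data** (Safety and feasibility): "Data for safety will be analysed as the number of sessions and exercises stopped due to pain", together with adverse events and MACCE. Feasibility covers recruitment rates, a recruitment-to-screening ratio, and "percentage of participants who complete the intervention, overall percentage of sessions attended and number of participants who drop out of the study".
- **Primary outcome** (abstract, Methods): "The primary outcome, cognitive function, will be assessed using the Alzheimer’s Disease Assessment Scale and cognitive subscale".
- **Aim** (Objectives): "This study aims to examine the effect of moderate-intensity resistance training compared to a control group". The same paragraph says the pilot data will inform the sample size of a definitive trial.
- **Criteria** (Data analysis): "The following parameters would indicate clinically important relative differences between groups". One item on the list that follows is a difference of 2 points or more on the ADAS-cog.

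**The concern.** Two summary measures are attached to data they do not suit.

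First, the ADAS-cog, the FDQ, lung function, muscular strength and the Four Square Step Test are all scores or measurements. A mean change in such a variable has no odds ratio. The wording also places the summaries within each group, whereas the aim and the 2-point criterion are both between groups. For outcomes first measured before surgery, a within-arm change to 14 weeks combines the effect of surgery, natural recovery and repeated testing with any effect of training. Only the randomised contrast separates these.

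Second, most of the feasibility and safety data are counts, percentages or events. The Sample size determination section names feasibility and safety as the focus of the study, so the form in which they are reported matters.

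At stake are the clarity of the pilot's estimates and what they contribute to planning the definitive trial.

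**Working it through.** **The plan's own figure.** There is none to reproduce. The minimum of 20 participants is set without a power calculation, and no SD, alpha or power is stated. The figures below are illustrations.

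**Inputs from the article**
- At least 20 participants (Sample size determination), allocated 1:1 (Randomisation, allocation concealment and blinding): 20 / 2 = 10 per arm.
- 80% retention: 20 × 0.8 = 16, or 8 per arm.
- ADAS-cog criterion: 2 points (Data analysis).

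**Assumption.** The article gives no ADAS-cog SD. I use a range of 2 to 6 points.

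**Step 1: can the named measure be set against the criterion?** The criterion is in ADAS-cog points and between groups. An odds ratio is a unitless ratio for a binary outcome, and the article defines no binary version of the ADAS-cog. Within-arm mean changes are in points but are not a contrast. What the criterion needs is the between-arm difference in means, and the article names no such estimator.

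**Step 2: what would the suitable estimate look like?** The 95% half-width for a difference in means is t(0.975, 2n − 2) × SD × √(2/n).
- n = 10 per arm: 2.101 × SD × 0.447 = 0.94 × SD, so 1.9 points (SD 2) to 5.6 points (SD 6).
- n = 8 per arm: 2.145 × SD × 0.5 = 1.07 × SD, so 2.1 points (SD 2) to 6.4 points (SD 6).

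The interval would be wide relative to 2 points over nearly all of this range. That is expected in a pilot, and reporting the interval makes it visible.

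**Step 3: what does the definitive trial need?** For a 2-point difference at 80% power and two-sided 5%, n per arm = 2 × (1.960 + 0.842)² × SD² / 2² ≈ 3.92 × SD².

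| Assumed SD | n per arm |
|---|---|
| 2 | 16 |
| 3 | 36 |
| 4 | 63 |
| 5 | 99 |
| 6 | 142 |

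The SD drives the answer, and an odds ratio supplies neither the SD nor the difference.

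**Step 4: mean ± SD for an event.** For x events in n participants, with p = x/n, the SD of the 0/1 indicator is √(p(1 − p) × n/(n − 1)). The comparison is the exact (Clopper-Pearson) 95% interval.

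| Events | Mean ± SD | Exact 95% interval |
|---|---|---|
| 0/10 | 0 ± 0 | 0 to 30.8% |
| 1/10 | 0.10 ± 0.32 (−0.22 to 0.42) | 0.3% to 44.5% |
| 2/10 | 0.20 ± 0.42 (−0.22 to 0.62) | 2.5% to 55.6% |

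For zero events the upper limit can be checked by hand: 1 − 0.025^(1/10) = 0.308. Mean ± SD either shows no uncertainty at all or runs below zero.

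**The case against.** The strongest reply is that this is a pilot that declares itself unpowered, ties the decision on a large trial to feasibility data, and is described here in a condensed article whose analysis plan is not shown. Descriptive analysis without tests is legitimate, and an unspecified model is no fault. All of that stands. It does not rescue the sentence on mean changes, because that sentence names a measure and the measure does not fit. An analysis plan would have to depart from it.

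Several stronger readings are tempting, and the article does not support them.

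- *The between-arm ADAS-cog comparison is never estimated.* The Data analysis section lists a between-group ADAS-cog difference as a criterion and specifies intention-to-treat analysis, and an odds ratio is itself a contrast. A comparison is intended; only a fitting estimator is unnamed.
- *The safety intervals are invalid.* No safety interval is specified. Confidence intervals appear only in the mean-change sentence. The fault is the choice of mean ± SD.
- *Zero events will be reported as 0 ± 0.* The Safety and feasibility section already plans counts and percentages, so this is only one reading of a loose parenthesis. Mean ± SD is also reasonable for per-participant quantities such as sessions attended.
- *The definitive trial's inputs are lost.* They are not. The SD can be computed from the same data, and subtracting the two arms' mean changes gives a difference. The point is that the plan does not say these will be reported.
- *Omitting baseline adjustment is an error of known size.* The plan proposes no change-score comparison to improve on. The variance ratio of baseline adjustment to change scores, (1 + r)/2, is 0.75 to 0.90 for an assumed correlation r of 0.5 to 0.8, but this is a large-sample figure. With 8 per arm, multiplying by 1 + 1/(2 × 8 − 4) = 13/12 for chance baseline imbalance gives about 0.81 to 0.98. Adjustment is a preference here.
- *Every outcome is confounded by surgery through its pre-operative baseline.* Strength and the Four Square Step Test are first measured at 2 weeks, before training starts (Table 1; Procedure and data collection), so the argument does not apply to them.

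**Conclusion.** The point holds in limited form. The only effect measure named does not fit the primary outcome or the other continuous outcomes, and it cannot be compared with the plan's own 2-point between-group criterion. Mean ± SD is assigned to feasibility and safety data that are mostly counts, percentages and events, for which it conveys no usable uncertainty.

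No stated figure is numerically wrong, and no go/no-go rule in the article uses the odds ratio. The consequence is limited to the pilot's reported estimates and its input to the definitive trial. The first part rests on the wording alone. The exact limits assume 10 participants per arm, and the half-widths and sample sizes assume an ADAS-cog SD of 2 to 6 points. A reader should not infer that the randomised comparison is absent or that any planned interval is invalid.

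**What to change.** Replace the two sentences in Data analysis, or settle the matter in the analysis plan before the data are analysed, as follows:

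1. **Continuous outcomes.** Report the between-group difference in means, with SD and 95% confidence interval, at 14 weeks and at the 6-month visit. Preferably adjust for the baseline value: the pre-operative value for ADAS-cog, FDQ and lung function, and the 2-week pre-intervention value for strength and the Four Square Step Test. Within-group summaries and graphs can stay as description.
2. **Events and proportions.** Report adverse events, MACCE and feasibility proportions as n/N with exact 95% confidence intervals.
3. **Per-participant quantities.** Keep mean ± SD for items such as sessions attended.
4. **Odds ratios or risk differences.** Use them only for binary outcomes, and name those outcomes.

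The cost is wording. It needs no new data, visits, participants or hypothesis tests. The Trial status section reports recruitment as finished, and the change is unaffected by that.

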### Data monitoring, harm and auditing

The team has nominated [name] to monitor all aspects of this project. As this is a small randomised trial without any interim analysis, there will not be a separate Data and Safety Monitoring Board. Any adverse outcomes will be reported via the CI [name] to the Melbourne Health HREC.

If a patient suffers any injuries or complications as a result of this research project, they will be advised to contact the study team as soon as possible and will be assisted with arranging appropriate medical treatment. If they are eligible for Medicare, they can receive any medical treatment required to treat the injury or complication, free of charge, as a public patient in any Australian public hospital.

In accordance with Melbourne Health HREC, details of patient enrolment, adverse events, withdrawal and study completion will be recorded in their electronic medical records. Annual reports will be submitted to facilitate their auditing and monitoring of registered trials.

## Discussion

The benefits of cardiac rehabilitation in optimising post-operative physical and functional recovery are well recognised globally. Exercise has also been shown to improve cognitive function. However, cognitive function is not assessed in the cardiac population pre-operatively, nor monitored post-operatively. Thus, the impact of cardiac rehabilitation on post-operative cognitive recovery is unknown.

Cardiac rehabilitation traditionally involves low-intensity aerobic exercise and at times low resistance weights [9]. Balachandran et al. [33] have shown that coughing produced the greatest sternal micromotion and pain when compared to dynamic upper limb and trunk tasks [33], whilst Swanson and LaPier have shown that common daily activity, such as moving from side-lying to sitting, opening doors and pulling out a chair require the movement of loads greater than that permitted by current sternal precautions [50]. However, despite evidence that demonstrates the safety of upper limb exercise in this population [33], resistance training is not typically commenced until 12 weeks post-operatively if at all, as current sternal precautions restrict the use of the upper limbs and trunk for 8–12 weeks [18, 51, 52]. As such, cardiac rehabilitation programs have been reported to adopt a conservative and cautionary approach to the prescription of upper limb exercises and in particular to resistance training of the upper limb. This inadvertently encourages patients to become physically inactive, potentially delaying their recovery and contributing to deterioration of physical and cognitive function. There is emerging evidence to support the safety and efficacy of moderate-intensity exercise, and upper limb and thoracic progressive exercise. Resistance training accelerates improvements in cardiovascular fitness and muscle strength and reduces inflammation, cognitive dysfunction and sarcopenia, which can persist for several months after surgery [11, 38, 53–59]. However, the effects of early moderate-intensity resistance training following cardiac surgery are unknown.

Cognitive impairment is a frequent complication of cardiac surgery that is not typically addressed in cardiac rehabilitation programs. There is evidence associating resistance-based exercise programs with improved cognitive outcomes in older adults (aged 65 years and older) [38, 60] and adults with mild cognitive impairment [41, 61], providing a strong rationale for incorporating resistance training into rehabilitation training after surgery. To our knowledge, this pilot study is the first trial to comprehensively assess the safety and feasibility, cognitive recovery, physical and functional recovery and participant perceived impact of early resistance training as a form of cardiac rehabilitation. The results of this pilot study will be used to determine the feasibility of a future large-scale randomised controlled trial that promotes the integration of early resistance training into existing aerobic-based cardiac rehabilitation programs in Australia.

### Trial status

Version 5, 17 December 2019

Recruitment commenced on 16 April 2018 and concluded on 31 August 2019.

## Data Availability

Requests for sharing of the trial protocol, full study report and anonymised participant-level dataset beyond that of the information detailed in this protocol will be considered on a case-by-case basis and made at the discretion of the research team.

## Abbreviations

MACCE: Major adverse cardiac and cerebral events
SIS: Sternal Instability Scale
RPE: Rating of Perceived Exertion
ADAS-cog: Alzheimer’s Disease Assessment Scale and cognitive subscale
MMSE: Mini Mental State Examination
IADL: Instrumental Activities of Daily Living
PostopQRS: Postoperative Quality of Recovery Scale
FDQ: Functional Difficulties Questionnaire
FSST: Four Square Step Test
BMI: Body mass index
FVC: Forced vital capacity
FEV1: Forced expiratory volume in 1 s
US: Ultrasound
